### 2.1. TEERMISO Study Patient Entry Criteria

#### 2.1.1. Describing Patient Groups

The clinical trial will include patients presenting with moderate to severe ischemic mitral regurgitation who may or may not require concomitant coronary artery bypass surgery (CABG) or percutaneous coronary intervention (PCI). Furthermore, patients will have undergone either S-SVRp or TMVp using TEER. Patients of any gender, race, or ethnicity will be eligible for inclusion in this study.

#### 2.1.2. Inclusion Criteria

-Age 18 years or older.-Chronic severe ischemic and non-ischemic mitral regurgitation (EROA ≥ 0.4 cm echocardiogram) with tethering as a major mechanism.-The occurrence of symptoms that indicate secondary mitral regurgitation (3+ or 4+ as determined by echocardiographic laboratory assessment) as an outcome of the development of cardiomyopathy, whether of an ischemic or non-ischemic etiology.-The management of the subject was conducted in accordance with the relevant clinical guidelines, including those pertinent to CAD, LV functional impairment, MR, and HF.-The procedure was conducted using either a standard surgical approach or a transcatheter technique for mitral valve repair.-Patients with atrial functional mitral regurgitation.-CAD in patients who underwent an S-MVi, with or without the need for coronary revascularization.-It will fall upon the cardiac team at each center to ascertain which patients to include in the register. The choice of treatment will be dependent on whether the patient received a standard surgical approach or a transcatheter technique for mitral valve repair.-In order to be included in the TEERMISO registry, it will be necessary for the individual in question to possess the capacity to sign both the informed consent and the Medical Information Release forms.

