## 4. Ethics and Dissemination

### 4.1. Implications for Treating Patients Undergoing Transcatheter Versus Standard Surgical Mitral Valve Operation for Secondary Mitral Regurgitation

A thorough examination of the data from this registry will yield current insights for a substantial number of SMR patients with a comprehensive follow-up period. The multicenter nature of this registry is expected to reduce the risk of bias related to institutional volume and surgical experience. It is anticipated that all participating centers will perform a minimum of 25 procedures per annum for SMR. Furthermore, a plan for mitral surgery must be devised and implemented, allowing for effective follow-up and management of late occurrences following replacement surgery or primary repair of SMR. It is anticipated that the data collected will yield insightful information regarding the influence of distinct surgical approaches on conventional mitral valve surgery and TEER. This will facilitate the evaluation of LV remodeling in long-term follow-up. Furthermore, this research will offer conclusive data on the effectiveness of various standard mitral valve surgical techniques in a setting where mortality rates are elevated, with a 50% mortality rate, as well as long-term mortality rates for patients who have undergone TEER.

A comparison of the results obtained from the analysis of S-SMVp, which involved three distinct procedures, and TMVp for use in SMR procedures, was conducted. The following comparative analysis is based on data from a multicenter dataset, which allows for a comprehensive overview of the findings. The objective is to identify the most effective intervention for left ventricular remodeling and enhanced left ventricular ejection fraction within a 10-year timeframe. It would be beneficial to ascertain whether there is a difference in the incidence of death from all causes at 10 years following S-SMVp or TMVp. It would also be advantageous to determine whether patients with increased LVEF also have more favorable HF symptoms. A related question is which of the two procedures (S-SMVp and TMVp) achieves an immediate reduction in MR to moderate or lower levels and what proportion of individuals can derive benefit from this result.

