**Inclusion Criteria**
Age 18 years or older. The patient presented with symptomatic secondary mitral regurgitation (3+ or 4+ by echocardiographic laboratory assessment), which was attributed to cardiomyopathy of either ischemic or non-ischemic etiology. The patient’s condition has been managed in accordance with the relevant clinical guidelines, including those pertaining to coronary artery disease, left ventricular dysfunction and disease, mitral regurgitation, and heart failure. Subjects with at least one hospitalization for heart failure. BNP ≥ 300 pg/mL or a corrected NT-proBNP ≥ 1500 pg/mL. NYHA functional class II or III or ambulatory class IV. Each center’s heart team will decide whether to offer MV surgery or TEER. Left ventricular end-systolic dimension ≤ 70 mm. Left ventricular ejection fraction ≥ 20% and ≤50%. The nature of the primary regurgitant jet is commissural or non-commissural. For the MitraClip group, the implanting investigator’s opinion is that the MitraClip can successfully treat the jet (if a secondary jet is present, it must be considered clinically insignificant). Trans-septal catheterization and femoral vein access is possible with the MitraClip implanting investigator. The subject gave written informed consent and agreed to all the terms of this study and the follow-up visits after the procedure.

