**Exclusion Criteria**
Life expectancy is less than 12 months due to noncardiac conditions. Excessive surgical risk (in the judgment of the surgical investigator). Patients who have undergone surgery on their mitral valve leaflet in the past, have a prosthetic mitral valve implanted, or have undergone a transcatheter mitral valve procedure prior to hospitalization. The subject must have undergone transcatheter aortic valve replacement (TAVR) within 30 days prior to hospitalization. Patients who have had mitral valve surgery, prosthetic in the past, have a prosthetic mitral valve implanted, or have undergone a transcatheter mitral valve procedure before. Surgery is required for tricuspid valve disease with the exception of tricuspid valve repair. Aortic valve disease that requires surgery or transcatheter intervention. Status 1 heart transplant or previous orthotopic heart transplantation. Patients requiring emergency or urgent surgery for any reason. Preoperative Congenital heart disease (except PFO or ASD). Patients for whom transesophageal echocardiography (TEE) is contraindicated or high risk. Echocardiographic evidence of intracardiac mass, thrombus, or vegetation. Patients with active endocarditis, active rheumatic heart disease, or leaflets degenerated from rheumatic disease (i.e., noncompliant, perforated). Active infections requiring current antibiotic therapy. Patients who are pregnant or plan to become pregnant within the next 12 months. A diagnosis of chronic obstructive pulmonary disease (COPD) necessitating the administration of continuous home oxygen therapy or chronic outpatient oral steroid use. The subject must not have undergone coronary artery bypass grafting (CABG) within 30 days prior to hospitalization for a TEER procedure. Subject hospitalization is not allowed if the individual has had a cerebrovascular accident within the last 30 days. Severe symptomatic carotid stenosis, as determined by ultrasound, is greater than 70%. ACC/AHA Stage D heart failure. Chronic renal insufficiency defined by Cr ≥ 2.5 or chronic renal replacement therapy (chronic hemo- or peritoneal dialysis). In the event that the calculated pulmonary artery systolic pressure (PASP) is determined to be greater than 70 mm Hg through the utilization of echocardiography or right heart catheterization, it is regarded as a high pressure unless active vasodilator therapy within the catheterization laboratory is capable of reducing the pulmonary vascular resistance (PVR) to a level below 3 Wood Units or between 3 and 4.5 Wood Units, with a v wave less than twice the mean of the pulmonary capillary wedge pressure. Structural heart diseases that can cause heart failure, excluding dilated cardiomyopathy of either ischemic or non-ischemic etiology. These diseases include hypertrophic cardiomyopathy, restrictive cardiomyopathy, and constrictive pericarditis. Infiltrative cardiomyopathies such as amyloidosis, hemochromatosis, and sarcoidosis. The patient is experiencing hemodynamic instability and requires inotropic support or mechanical heart assistance. The echocardiogram shows moderate or severe right ventricular dysfunction, indicating physical evidence of right-sided congestive heart failure. Implant of any Cardiac Resynchronization Therapy (CRT) or Cardiac Resynchronization Therapy with a cardioverter–defibrillator (CRT-D) within the last 30 days prior hospitalization. The mitral valve orifice area should be assessed by a transthoracic echocardiogram (TTE) within 90 days prior to subject hospitalization and should be less than 4.0 cm^2^. Modified Rankin Scale ≥ 4 disability.

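### Groups follow the procedure received, and TEER-only suitability criteria need not predate the procedure, so aborted or converted TEER attempts can leave the TEER denominator

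*Protocol article*

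**What the plan says.** Two places in the protocol article tie the group to the procedure carried out. Section 2.1.1 requires that "patients will have undergone either S-SVRp or TMVp using TEER". Section 2.1.2 states: "The choice of treatment will be dependent on whether the patient received a standard surgical approach or a transcatheter technique for mitral valve repair". Read literally, that sentence makes the choice of treatment depend on its own result. The only workable reading is that group membership follows the treatment received. The same item leaves it to each center's cardiac team to decide which patients enter the register.

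Table 4 uses a different basis. Each center's "heart team will decide whether to offer MV surgery or TEER". It then adds two conditions that concern TEER alone:

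- "For the MitraClip group, the implanting investigator’s opinion is that the MitraClip can successfully treat the jet"
- "Trans-septal catheterization and femoral vein access is possible with the MitraClip implanting investigator"

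The nearest surgical counterpart is an exclusion, "Excessive surgical risk (in the judgment of the surgical investigator"). It concerns operative risk rather than expected success, and it is not confined to one group.

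The text after the exclusion list in section 2.1.3 says that the cohort came from the databases of the five centers and was screened for eligibility. The article does not say how to classify a TEER attempt that ends without a clip or is converted to surgery.

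**The concern.** Offered, started and received coincide for most patients. They differ for those in whom TEER was begun and abandoned, or begun and followed by surgery in the same stay, and these patients are likely to have poor results. If the group is fixed by what was received, and the TEER suitability opinion can be formed while screening past cases, the procedural result can influence who counts as a TEER patient.

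Section 4.1 asks which procedure "achieves an immediate reduction in MR to moderate or lower levels and what proportion of individuals can derive benefit from this result". That proportion depends directly on the denominator. Mortality, MACE and LVEDVI are compared between the same groups. Section 3 relies on propensity weighting combined with regression to estimate a causal effect. Those methods balance baseline covariates among the patients who are in the data set. They cannot restore patients left out because of how the procedure went.

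**Working it through.** **Step 1. Apply the text to the cases where the rules differ.**

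| Case | Section 2.1.2 (received) | Table 4 |
|---|---|---|
| TEER started, no clip placed | Open: the technique was used, but no repair was received | Offered TEER. Meets the opinion and access items if judged beforehand; may fail them if judged afterwards |
| TEER converted to urgent surgery | Can be read as surgical | Emergency or urgent surgery is excluded, so the case may fall out of both groups |
| TEER, then non-urgent surgery in the same stay | Can be read as surgical | One exclusion covers a transcatheter mitral procedure before hospitalization; a second has no such limit and on its face bars the case |
| TEER completed, mitral surgery later | TEER | Stays in TEER; re-intervention is a MACE component and reoperation is analysed as time to event (section 2.3) |

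Loss from the TEER group is possible in the first three rows. Entry into the surgical group is largely blocked. Loss from both groups is possible in rows two and three.

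**Step 2. Size, by assumption only.** The article has no rate of aborted or converted TEER and no success rate for either group, so there is no figure of its own to reproduce on this point. Let f be the share of TEER attempts aborted or converted, p the success rate in completed cases and q the success rate in failed attempts.

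- True rate per attempt: (1 − f)p + fq
- Rate if failed attempts are left out: p
- Inflation: p − [(1 − f)p + fq] = f(p − q)

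With p = 50% (assumed):

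| f | q = 0% | q = 20% |
|---|---|---|
| 2% | 1.0 point | 0.6 |
| 5% | 2.5 | 1.5 |
| 10% | 5.0 | 3.0 |
| 15% | 7.5 | 4.5 |

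For immediate MR reduction a higher p may be more natural. With p = 90% and q = 0 (assumed), the rate per attempt is 0.95 × 0.90 = 85.5% at f = 5%, an overstatement of 4.5 points. At f = 10% it is 0.90 × 0.90 = 81%, an overstatement of 9 points. If q = p, the inflation is zero.

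**Step 3. A yardstick.** Section 3 gives 384 surgical and 246 TEER patients (384 + 246 = 630), 80% power and two-sided alpha 0.05, but no effect size. Solving backwards, the smallest detectable standardized difference is (1.960 + 0.842) × √(1/384 + 1/246) = 0.229 SD. For a remodeling rate of 50% under surgery (assumed), it is about 11.4 percentage points. The p = 50% range in step 2 stays below that, but its upper part is a sizeable fraction of it.

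**Step 4. A mortality illustration.** Take 246 TEER attempts, 12 of them failed with 40% one-year mortality, and 15% mortality in everyone else (all assumed). By attempt, TEER mortality is (234 × 0.15 + 12 × 0.40)/246 = 39.9/246 = 16.2%, against 15.0% for surgery. If the 12 are left out, both groups show 15.0%, and a difference of 1.2 points disappears.

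**The case against.** The strongest reply is that the article never says failed attempts are dropped. The Abstract promises consecutive enrolment, and an attempted TEER can be read as having undergone the transcatheter technique. The MitraClip items are worded as candidacy, not result: a patient judged treatable whose procedure then failed still meets them. Saying who decides on treatment (Table 4) and what was received (section 2.1.2) need not be a contradiction in a registry. Detailed analysis-set rules may also sit in a full protocol or supplement that is not shown.

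Much of this stands. It rules out stating as fact that failed attempts are removed. It does not close the gap, because the article prints a grouping rule based on receipt, prints a second basis beside it, and leaves the suitability opinion undated in a cohort screened from existing records. Five centers can apply that wording differently and each be compliant.

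A reader might go further and infer that converted cases move into the surgical group and worsen its results. In the mortality illustration, that would give surgery (384 × 0.15 + 12 × 0.40)/396 = 62.4/396 = 15.8% against 15.0% for TEER and reverse the sign. The documents do not support this as the expected course. The urgent-surgery exclusion and the prior-transcatheter exclusion without a hospitalization limit largely block that route.

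**Conclusion.** The point holds as a risk of bias in favour of TEER created by the stated grouping rule and the one-sided, undated suitability criteria. The route that the text leaves open is loss of aborted or converted attempts from the TEER denominator, and sometimes from both groups. The direction assumes that failed attempts do worse than completed ones.

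A reader might infer that the TEER results are inflated. The documents do not show that: no failure or conversion rate and no outcome after failure is given, so neither the occurrence nor the amount can be established. The 0.6 to 7.5 points are conditional on f between 2% and 15%, p = 50% and q between 0% and 20%. The immediate MR-reduction proportion is the result most directly exposed. The primary endpoint, LVEDVI at 10 years, is exposed through the same group definition.

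**What to change.** 1. Reconcile section 2.1.2 with Table 4 by defining each patient's group as the first mitral procedure started, with the start stated in operational terms (for example venous puncture for TEER and skin incision for surgery).
2. Identify TEER cases from each center's procedure log.
3. Keep aborted and converted cases in the group in which they started, and report abortion and conversion as an outcome.
4. Keep the TEER suitability and access criteria, but apply them only as documented before the procedure. Deleting them would change the population and worsen overlap between the groups. Assess the Table 4 exclusions at the same point in time, so that a conversion does not itself trigger one.
5. Show the as-received grouping as a sensitivity analysis.

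The cost is a change of wording, some extra log and chart checking at five centers, and possibly a slightly lower reported TEER success rate. Clinical care is not affected.

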## Abstract

**Background:** Secondary mitral regurgitation (SMR) is characterized by a pathological process impacting the left ventricle (LV) as opposed to the mitral valve (MV). In the absence of structural alterations to the MV, the expansion of the LV or impairment of the papillary muscles (PMs) may ensue. A number of technical procedures are accessible for the purpose of determining the optimal resolution for MR. Nevertheless, there is a dearth of rigorous data to facilitate a comparative analysis of MV replacement, MV repair (including subvalvular repair), and transcatheter mitral valve interventions (TMV-Is). The objective of this investigation is to evaluate and compare the efficacy and clinical outcomes of transcatheter mitral valve repair (TMV-r) utilizing the edge-to-edge mitral valve repair (TEER) procedure in comparison to conventional surgical mitral valve interventions (S-SMVis) in patients with secondary mitral regurgitation. **Methods and analysis:** A consortium of five cardiac surgery institutions from four European states and Japan have joined forces to establish a multicenter observational registry, designated TEERMISO. Patients who underwent technical procedures for SMR between January 2007 and December 2023 will be enrolled consecutively into the TEERMISO registry. The investigation team evaluated the comparative efficacy of replacement and repair techniques, utilizing both the standard surgical methodology and the transcatheter intervention. The primary clinical outcome will be the degree of left ventricular remodeling, as assessed by the left ventricular end-diastolic volume index, at 10 years. The forthcoming research will assess a variety of secondary endpoints, among which all-cause mortality will be the primary endpoint. Subsequent assessments will be made in the following order: functional status, hospitalization, neurocognition, physiological measures (echocardiographic assessment), occurrence of adverse clinical incidents, and reoperation. **Ethics and dissemination:** The multicenter design of the database is anticipated to reduce the potential for bias associated with institutional caseload and surgical experience. All participating centers possess an established mitral valve protocol that facilitates comprehensive follow-up and management of any delayed mitral complications following replacement surgery or surgical repair of the secondary mitral regurgitation. The data collected will provide insights into the impact of diverse surgical approaches on standard mitral valve surgery and TEER. This will facilitate the evaluation of LV remodeling over the course of long-term post-procedural follow-up. **Trial Registration:** ClinicalTrials.gov ID: NCT05090540; IRB ID: 202201143

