## 2. Methods and Analysis

The TERMISIO prospective observational registry encompasses individuals who have been subjected to technical procedures and treatments for SMR at five cardiac surgery centers located in two European nations (France and Italy) and Japan (Table 3) over the course of nine years, from 1 January 2014 to 31 March 2023. The objective of this study is to collate data on patients who had undergone treatment during the specified period.

The goal is to obtain additional data for the purpose of future clinical research on the topic in question. The data pertaining to the successive patients with SMR will be compiled in an Access database created using Microsoft Access software, developed by Microsoft in its Redmond, Washington, USA, headquarters. The data sheet will comprise a set of predetermined variables, including those pertaining to the baseline, surgical procedure, and postoperative course of the patients. Prior to the commencement of this study, permission will be sought from the relevant institutional review board or local ethical committee in accordance with the legislation of the country in which this study is to be conducted.

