#### 2.1.3. Exclusion Criteria

-Pediatric.-Any echocardiographic evidence of structural (chordal or leaflet) mitral valve disease.-Papillary muscle rupture.-Infective endocarditis.

A review of the clinical facilities participating in this investigation suggests that the aggregate sample size will be 630. The patient cohort was derived from the databases of the five participating centers, which were subjected to a rigorous screening process to ascertain their eligibility for integration into the analytical framework (Supplementary Material). A combination of monitoring strategies will be employed to oversee the patients, which may include the dissemination of information by mail to the referring physicians of patients who underwent a procedure at the hospitals, direct observation at the center of the surgical procedure, and follow-up telephone interviews with the healthcare providers where the patients were readmitted due to post-procedural complications. The research team conducted periodic assessments of the actual inclusions in comparison to the pre-specified targets. The implementation of a uniform protocol across all centers enabled the documentation of the number of patients who underwent a range of interventions and who were subjected to echocardiographic and clinical follow-up.

The repository of data encompasses information pertaining to the participation of females and ethnic minorities in scientific investigations, specifically clinical trials. This is important for a number of reasons, including those of a scientific, ethical, and social nature, as well as with a view to ensuring the generalizability of the results of the studies conducted. The TEERMISO consortium is dedicated to achieving scientific objectives while ensuring an equitable recruitment of patients, regardless of gender or ethnicity. A minimum of 30% of the TEERMISO registry participants are women, and 25% are from minority ethnic groups. In order to ensure the appropriate representation of these groups, the recruitment centers must implement two measures. Firstly, the number of females and ethnic minorities chosen and enrolled through the screening and exclusion procedures must be recorded. Secondly, these figures must be overseen by each clinical facility on an annual basis. The criteria for inclusion and exclusion of patients who have undergone technical procedures for secondary mitral regurgitation are outlined in the following section (Table 4).

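### Entry requires consent, but the cohort was already treated and consent is undated: for patients approached after the procedure, earlier deaths drop out of the outcome analyses

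*Protocol article*

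**What the plan says.** **Consent as an entry condition.** Section 2.1.2 makes it necessary for a participant "to possess the capacity to sign both the informed consent and the Medical Information Release forms". The inclusion list in Table 4 goes further: "The subject gave written informed consent and agreed to all the terms of this study and the follow-up visits after the procedure". Neither list exempts deceased or incapacitated patients.

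**A cohort already treated.** Section 2.1.3 states: "The patient cohort was derived from the databases of the five participating centers". Section 2 describes the aim as collating data on people treated during the study period, with ethics permission to be sought before the study begins. The treatment period is given twice, differently. The Abstract says "Patients who underwent technical procedures for SMR between January 2007 and December 2023 will be enrolled consecutively into the TEERMISO registry", while Section 2 says "over the course of nine years, from 1 January 2014 to 31 March 2023".

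**Who decides on inclusion.** Section 2.1.2 also says "It will fall upon the cardiac team at each center to ascertain which patients to include in the register". The Abstract sentence above describes consecutive enrolment.

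**What is analysed.** All-cause death is the main secondary endpoint (Sections 2.2.2 and 2.3), and Section 4.1 compares it at 10 years after the procedure. MACE includes death and stroke, and 30-day readmission is counted from the procedure. Section 3 plans inverse probability weighting by propensity score with doubly robust regression. It does not mention delayed entry.

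**The concern.** A consent requirement is harmless when the form is signed at or before the procedure. It becomes a survival requirement when the form is signed later. A patient who died, or who was left unable to sign, in the interval can never enter. A patient who does enter brings a stretch of follow-up in which death was impossible by construction.

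For these patients, observed deaths before signature are zero. Non-fatal early events, such as a stroke or a 30-day readmission, are under-represented to the extent that they precede death or loss of capacity.

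The planned adjustment does not reach this. Propensity weights balance baseline covariates among patients in the data set. They cannot stand in for patients removed because of what happened after treatment.

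The cardiac-team sentence raises a related question. If the team may choose whom to include, enrolment is not consecutive. If it only verifies eligibility, the sentence should say so.

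**Working it through.** **Inputs from the article**
- Window A: 1 January 2014 to 31 March 2023, L = 9.25 years (Section 2).
- Window B: January 2007 to December 2023, L = 17 years (Abstract).
- Mortality: 50%, with no time point (Section 4.1).

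The article gives no figure for deaths before consent, so there is nothing of its own to reproduce on this point. Its sample size adds up (384 + 246 = 630), but the point does not depend on it.

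**Assumptions (not in the article)**
- The 50% is 10-year mortality; 30% and 70% are tried as well.
- Hazard is constant and accrual is uniform over the window.
- Consent is sought at window close, or a = 1 year later.

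**Formula.** With hazard λ = −ln(1 − m)/10 for 10-year mortality m, the share dead before consent is

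1 − e^(−λa) × (1 − e^(−λL)) / (λL).

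**Central case.** m = 0.50 gives λ = 0.0693 per year, and a = 0.
- Window A: λL = 0.641, so (1 − 0.527)/0.641 = 0.738 are alive and **26%** are dead.
- Window B: λL = 1.178, so (1 − 0.308)/1.178 = 0.587 are alive and **41%** are dead.

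**Range: share dead before consent**

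| Assumed 10-year mortality | A, at close | A, +1 year | B, at close | B, +1 year |
|---|---|---|---|---|
| 30% | 14.8% | 17.8% | 25.0% | 27.6% |
| 50% | 26.2% | 31.1% | 41.3% | 45.2% |
| 70% | 39.7% | 46.5% | 57.5% | 62.3% |

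**Effect on a naive 10-year estimate.** Take Window A, 50%, consent at close. Everyone is less than 10 years from the procedure at close, so every 10-year survivor is also alive to sign. Among signers, 10-year survival is 0.50/0.738 = 0.68, and apparent mortality is 32% instead of 50%.

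**Effect on the comparison.** This cannot be computed from the article, which gives neither early mortality by arm nor the calendar spread of each procedure. A simulation of Window A with 400,000 patients per arm, rates counted from the procedure and consent at close, shows how much depends on those inputs:
- Equal hazards and equal accrual leave the TEER/surgery rate ratio at 1.00.
- Equal hazards, with TEER placed in the later half of the window, move it from 1.00 to about 1.37.
- Invented 30-day mortality of 5% (surgery) and 2% (TEER), with equal accrual, moves it from 0.94 to 1.00.

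The last two rest on inputs that the article does not supply.

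**The case against.** The strongest reply is that consent may have been taken at the time of treatment. Section 2 opens with "The TERMISIO prospective observational registry encompasses individuals who have been subjected to technical procedures and treatments for SMR", and the Abstract describes consecutive enrolment. Table 4 has patients agreeing to visits after the procedure. Capacity to sign can be read as a condition at the procedure. The Abstract also lists an IRB number, although Section 2 speaks of permission still to be sought. This part stands: a reader might infer that early deaths are excluded by rule, but the article does not establish that, because it never dates consent. The reply does not remove the problem. Consent to the terms of this study is hard to place at procedures done years before the study had permission, and the database-derived cohort points to later contact.

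Second, the cardiac-team sentence may mean checking eligibility. It shares an item with the choice of treatment, and the corresponding Table 4 item concerns only which procedure to offer. That reading is fair. Nothing says that the team chooses patients once their outcome is known. The text conflicts with consecutive enrolment but does not prove selection.

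Third, a reader might take procedure volume as proof of selection. Section 4.1 expects that "all participating centers will perform a minimum of 25 procedures per annum for SMR". Then 5 × 25 × 9.25 = 1,156 procedures, or 5 × 25 × 17 = 2,125, of which 630 would be 54% or 30%. The article does not support this use. The figure is an anticipated minimum and not past throughput, it covers all SMR procedures, and Table 4 excludes many patients. The gap says nothing about survival.

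Finally, screening detail may sit in the supplement or the full protocol. That excuses missing logs, but it does not excuse an entry rule that conflicts with the stated source of patients.

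**Conclusion.** The concern holds in this form: entry is conditional on consent without exception for the dead or incapacitated, the cohort is described as already treated and database-derived, and the timing of consent is not given. For every patient approached after the procedure, mortality, MACE and 30-day outcomes lose early events, and the planned weighting cannot correct this.

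The 26% and 41% are illustrations. They rest on reading the 50% as 10-year mortality, on constant hazard and uniform accrual, and on consent at window close. Under the wider assumptions the share is about 15% to 62%. If all consent was contemporaneous, it is zero.

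A reader might go on to infer that the loss differs between surgery and TEER and so favors one of them. That is possible, but the article gives no arm-specific early mortality or treatment dates, so neither the size nor the direction of bias in the comparison is known.

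**What to change.** 1. In Section 2.1.2 and Table 4, define the cohort as all consecutive patients who met the criteria at the procedure date, and limit the cardiac team's role to verifying eligibility. This also reconciles Section 2.1.2 with the Abstract.
2. Limit signed consent to living patients contacted for new data. Include the existing records of deceased patients by an ethics-approved route where local law allows.
3. State when consent is obtained relative to the procedure, and report deaths before consent by arm.
4. Where a center cannot do this, start its risk time at the consent date (left truncation, in both Kaplan-Meier and Cox analyses) and leave that center out of 30-day outcomes. Say how the propensity weights are then built: weights fitted only among patients who survived to consent need not balance the arms at the procedure.

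The cost is protocol wording, a request to the ethics committees and a delayed-entry analysis with some care over the weights. The downside is less early risk time from centers without an approved route.
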